# Study procedures

## Participant recruitment

Recruitment will occur via nursing staff (Breast Care Nurses, Cancer Care Coordinators and other nursing staff) working at each of the participating hospitals. Staff will briefly inform each patient about the study (using a standard script; appendix a) and provide patients with a study information pack during a routine consultation (e.g. pre/post-surgery; beginning, mid or end of adjuvant treatment). In addition, interested cancer clinicians (surgeons, oncologists, radiologists) will provide patients at participating hospitals (Royal Brisbane and Women’s Hospital, Mater Adult Hospital, Mater Private Hospital, Redcliffe Hospital, Greenslopes Private Hospital, North West Private Hospital, Holy Spirit Northside Private Hospital) with a study information pack. The information pack will contain a Patient Information Brochure (appendix b) and Consent to Contact Form (appendix c) and reply-paid envelope. Women interested in finding out more information are instructed to complete the Consent to Contact Form and either hand it back to their nurse or clinician or post it back to the research team in the reply-paid envelope.

To identify women who were treated prior to recruitment commencing, nursing staff and volunteers under their direction at approving hospitals will send a letter to patients diagnosed within the previous two years about the study. Nursing staff and/or volunteers with approval to access hospital data will go through records of patients and make a list of patients who were diagnosed within the previous two years. A password-protected excel spread sheet containing the patients’ details (given names, surname, sex, date of birth, address, date of last contact) will be emailed from the hospital to the Registrar of the Health Statistics Unit for cross-checking against the Queensland Deaths Register – this will enable the identification of any deceased patients. Once the death matching has been completed, the password-protected spread sheet will be emailed back to the hospital staff identifying any deceased patients. These patients will then be excluded from the list of patients to be included in the study mail-out.

Hospital volunteers will then compile letters to be sent out to patients. This mail-out will include the following materials:

- Letter to the patient on hospital letterhead from their nurse
- Patient information brochure
- Consent to contact form
- Reply-paid envelope addressed to the research team

Study posters may also be placed in the appropriate clinic(s) at each of the hospitals. The posters instruct interested patients to contact the project manager directly. Other potentially eligible women may also hear about the study through word-of-mouth or media. These women may contact the project manager directly.

Interested woman who complete and return the Consent to Contact Form or contact the project manager directly will then be posted a Participant Information Sheet (appendix d) and Participant Consent Form (appendix e), which outlines in detail what the study is about, what participation would involve, benefits and risks of participation and provides contact details for the research team. A member of the research team will then telephone interested women within 7 days to screen for eligibility (appendix f), enable women to ask questions and determine their interest in participating. Women who would like to participate are encouraged to sign and return the Participant Consent Form (appendix e). Participation in the study will not commence until written informed consent is received.

Women who are still undergoing treatment (chemotherapy and/or radiotherapy) but who are potentially eligible and interested in the study will provide an estimated date of treatment completion which will be recorded in the study database. The women will then receive another telephone call after this date to again screen for eligibility, answer questions and determine interest (appendix f).

Women interested in taking part in the study are asked if they know anyone currently participating in the study during Screening and Recruitment call. If they have a close friend or relative already in the study who they maintain close contact with, women will be allocated to the same study group to prevent contamination.

Figure 2 provides an overview of the recruitment procedure.

Nursing staff (breast care nurses, cancer care coordinators) and interested cancer clinicians (surgeons, oncologists, radiologists) outline study & give patients from seven participating hospitals ‘Patient Information Brochure’ and ‘Consent to Contact Form’

Interested patients complete and return ‘Consent to Contact Form’ to project team or contact project manager directly

Patient details entered into study database, patient posted ‘Participant Information Sheet’ and ‘Participant Consent Form’

Project member telephones patient to screen for eligibility (finished treatment, breast cancer stage, contraindications to participation, BMI, sufficiently fluent in English) and gain informed consent to participate

Consent

Ineligible

Refusal

Treatment not completed

Signed ‘Participant Consent Form’ received

Patient estimated date for treatment completion recorded in database; recall after this date

Baseline assessment

Randomisation

Intervention

Usual care

**Figure 2.** Recruitment Flowchart

Identifying newly diagnosed breast cancer patients through the Queensland Cancer Registry

From 1 July 2013, a change in recruitment protocol will be implemented whereby recruitment will primarily occur through the Queensland Cancer Registry (QCR). Breast cancer patients diagnosed from 1 July 2013 to 30 June 2014, residing within a 100km radius of Brisbane, will be identified via electronic pathology reports held within the QCR. Recruitment will follow standard Queensland Cancer Registry protocol for recruitment of cancer patients following approval of a Public Health Act 2005 application by the Director-General of Queensland Health.

Patients diagnosed from 01 July 2013 to June 2014 and meeting the following criteria will be identified via QCR’s electronic pathology reports database:

- Breast Cancer (no evidence of DCIS or metastatic disease)
- Female
- Aged 25*-75 years (an existing study is identifying cancer patients aged up to 24 years through the Queensland Cancer Registry during the period of access requested)
- Residing within 100km radius of Brisbane CBD

Vital status will be checked for all identified patients by QCR staff using approved methods. Patients will then be sent a Patient Letter (on QCR letterhead), Patient Information Brochure and Consent to Contact Form with a reply-paid QCR envelope. Note: a different version of the Consent to Contact Form has been developed to be sent to patients identified through the QCR (Consent to Contact Form; version 2, modified 12 06 13). This version of the Consent to Contact Form instructs patients to complete the form to indicate either that they agree to be contacted about the study or that they do not wish to be contacted about the study. Patients who do not return the Consent to Contact form within 21 days will be sent a follow-up letter from the Registrar, on behalf of the researchers, as per standard QCR patient recruitment protocol. Patients who return the Consent to Contact form to state that they do not wish to be contacted will receive no further contact.

Once a patient’s Consent to Contact Form has been received and sighted by the Registrar, the Registrar will give permission for the researchers to take Consent to Contact Forms of patients who indicated that they agree to be contacted out of the QCR and back to the Cancer Prevention Research Centre (UQ). Interested women will be posted a Participant Information Sheet and Participant Consent Form and then telephoned by a member of the research team to screen for eligibility and elicit informed consent, as per the original recruitment protocol outlined above.

Amended hospital recruitment protocol

As patients diagnosed from 1 July 2013 to 30 June 2014 will be identified through the QCR, hospital recruitment protocol will be amended to allow for nursing staff and doctors within previously approved hospital sites to disseminate study information packs to breast cancer patients diagnosed prior to 1 July 2013. This will enable women diagnosed prior to 1 July 2013 returning to the hospital for adjuvant treatment or follow-up consultations to be informed about the study. In addition, study posters will continue to be displayed at approved hospital sites to allow interested women who have not been informed about the study by their nurse or doctor to contact the project manager to find out more information about the study.

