## Study design

**Design:** This is a randomized controlled trial, with participants randomly allocated to one of two groups: 12-month weight loss support intervention or usual care.

**Data Collection:** Data collection points occur at baseline, 6-months (short-term), 12-months (end-of-intervention) and 18-months (maintenance post-intervention).

See Figure 1 for an overview of the study design

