## Allocation method

Participants will be allocated to either the Intervention group of the Usual Care group following completion of baseline data collection. A staff member who does not work on the study will create a computer-generated randomisation plan using uneven block sizes ([www.randomization.com](http://www.randomization.com)). This staff member will be notified when participants have completed baseline assessment and will allocate the participant IDs to either the usual care group or the intervention group based on the randomisation plan.

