## Blinding

The group allocation sequence will be concealed from staff involved with participant recruitment (group allocation will be conducted by a staff member not involved with the study). Once allocated to the study group, the project manager and participants will not be blinded to the group allocation (as is the case with most lifestyle based interventions). Staff involved with data collection will remain blinded to the participants’ group allocation.

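### The protocol lets a woman with a close friend or relative already in the trial be placed in that person's arm instead of being randomised, so she can know her arm before she consents

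*Protocol*

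**What the plan says.** Protocol section 5.1 (Participant recruitment) sets the rule. The question comes at the screening stage: "Women interested in taking part in the study are asked if they know anyone currently participating in the study during Screening and Recruitment call". For a candidate in regular touch with such a friend or relative, the stated consequence is this: "women will be allocated to the same study group to prevent contamination". In the same section, consent comes at or after that call: "Women who would like to participate are encouraged to sign and return the Participant Consent Form". Figure 2 gives the same order: telephone screening, receipt of the signed form, baseline assessment, randomisation.

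Other sections describe allocation without this exception. Section 3.3 (Study design): "This is a randomized controlled trial, with participants randomly allocated to one of two groups". Section 5.2 (Allocation method) says that a staff member outside the study "will allocate the participant IDs to either the usual care group or the intervention group based on the randomisation plan". Section 5.3 (Study Groups) repeats that participants are randomly allocated.

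Section 5.4 (Blinding) has two relevant statements. Before allocation, "The group allocation sequence will be concealed from staff involved with participant recruitment". After it, "the project manager and participants will not be blinded to the group allocation".

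**The concern.** A woman placed under the section 5.1 rule is not randomised. Nothing about her arm is left to chance once her friend or relative has been allocated.

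Her arm is also not concealed from her. The two arms are easy to tell apart from a participant's account: 22 coaching calls with a workbook, scales and a pedometer in one, and brochures, a newsletter and brief feedback in the other. A candidate linked to a usual-care participant can decline. A candidate linked to an intervention participant can join because she wants the coaching. Motivation plausibly predicts weight loss, so women who enter in this way may differ between the arms for reasons unrelated to treatment. The likely direction favours the intervention, although nothing in the protocol proves it.

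Randomisation and concealment cannot be restored for these women once they are enrolled. An analysis plan could leave them out, but only if they can be identified, and the protocol does not ask for them to be recorded as a separate group.

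**Working it through.** **1. The texts side by side**

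| Question | Section 5.1 | Sections 3.3, 5.2, 5.3 |
|---|---|---|
| What fixes the arm? | The friend's or relative's arm, for linked women | The randomisation plan, for all participants |
| Is an exception stated? | Yes | No |

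Both cannot hold for a linked woman.

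**2. Can she know her arm before consent?**

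- The link is raised at the screening and recruitment call (5.1).
- The signed form, baseline assessment and allocation come later (5.1, Figure 2).
- Her friend or relative, once allocated, knows her own arm (5.4).

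So the information can reach the candidate before she signs. Two conditions apply. The friend must already have been allocated, and the candidate must know or guess the rule. The protocol does not say whether she is told.

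**3. The plan's own sample size**

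Inputs from section 8.1.1: difference 5 points, SD 8.5, two-sided 5%, power 90%, attrition 25%, 80 per group.

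- n per group = 2 × 8.5² × (1.960 + 1.282)² / 5² ≈ 60.7, so 61 evaluable.
- 61 / 0.75 = 81.3, so 82 enrolled, which is within 2 women of the stated 80.
- With 80 × 0.75 = 60 evaluable per group, the SE is 8.5 × √(2/60) = 1.55 points and power is 89.7% (normal approximation).

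The stated size reproduces and is not in dispute.

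**4. Possible bias (assumed inputs)**

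The protocol gives neither the number of linked women, k, nor a prognostic gap, g, between linked women in the two arms. If they are spread evenly over the arms, bias = (k/160) × g.

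| k (assumed) | g (assumed) | Bias, points |
|---|---|---|
| 2 | 2 | 2/160 × 2 = 0.025 |
| 4 | 4 | 4/160 × 4 = 0.1 |
| 24 | 4 | 24/160 × 4 = 0.6 |

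If all linked women sat in one arm and differed from its randomised women by b points, that arm's mean would shift by k × b/80. For example, 8 × 5/80 = 0.5 points, which is of the same order. Against the SE of 1.55, a bias of 0.1 is 0.06 SE and a bias of 0.6 is 0.39 SE. The latter would raise the two-sided type I error from 5% to about 6.7%.

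**5. Power if linked women are excluded and not replaced**

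Evaluable n per arm = (160 − k)/2 × 0.75; power = Φ(5 / (8.5 × √(2/n)) − 1.96).

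| k excluded (assumed) | n per arm | Power |
|---|---|---|
| 0 | 60 | 89.7% |
| 8 | 57 | 88.1% |
| 16 | 54 | 86.4% |
| 24 | 51 | about 84% |

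**The case against.** The strongest reply is that the rule is conditional and will rarely apply. A linked woman needs a close contact who has herself met the stage, age, BMI, treatment and time-since-diagnosis criteria and has already enrolled, while recruitment draws on several hospitals and a registry covering a 100 km radius. With 2 to 4 such women the hypothetical bias is at most about 0.1 points. Preventing contamination is also a legitimate aim. This stands: the number is unknown and probably small, although section 5.1 also admits women who hear of the study by word of mouth, the route on which links are most likely.

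A reader might infer more than the text supports in four ways.

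- *That the trial contains non-randomised women.* The protocol permits them. It does not show that there are any.
- *That they count towards the 160.* Section 5.5 recruits until 160 women have been randomised. Read literally, that leaves out women placed by the rule. The text does not settle the matter.
- *That the recruiting caller knows the arm, so that section 5.4 is contradicted outright.* Section 5.4 conceals the sequence, and learning of a link does not reveal the sequence. It names only the project manager and participants as unblinded, and nothing says that the caller knows the friend's arm. The supported point is that the candidate may know.
- *That the primary model is wrong because it ignores correlation within linked pairs.* The effect is minor, and an analysis plan that is not shown here may deal with it.

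None of this removes the conflict between section 5.1 and sections 3.3, 5.2 and 5.3, or the loss of concealment for a woman to whom the rule applies.

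**Conclusion.** The point holds as a contradiction about how women are allocated, with a loss of concealment for those affected. Following section 5.1 as written would admit women whose arm is not set by the randomisation plan and who can know it before consenting. Selective enrolment is then possible, plausibly in favour of the intervention.

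The size cannot be derived from the protocol. A range of 0.03 to 0.1 points for 2 to 4 women, rising to 0.6 points for 24, rests wholly on assumed counts and an assumed gap of 2 to 4 points. A reader might infer that the trial's conclusion is in danger. These figures do not show that, since even the extreme is well below the 5-point target. The case for correction rests on the integrity of allocation, which cannot be repaired after enrolment, and on how little the change costs.

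**What to change.** - Amend sections 5.1 and 5.2 to state that women placed by the friend-or-relative rule are not randomised, are flagged in the study database at entry, do not count towards the 160 randomised, and are excluded from the primary comparison.
- Specify a sensitivity analysis that adds them back.
- Reword sections 3.3, 5.3 and 5.4 to acknowledge the exception, including that concealment does not extend to these women.

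The aim of avoiding contamination is kept, because linked women can still join their contact's group. The cost is protocol wording, a database flag, and either the modest loss of power shown in the working or the recruitment, assessment and, where applicable, coaching of as many further women as are excluded.

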## Allocation method

Participants will be allocated to either the Intervention group of the Usual Care group following completion of baseline data collection. A staff member who does not work on the study will create a computer-generated randomisation plan using uneven block sizes ([www.randomization.com](http://www.randomization.com)). This staff member will be notified when participants have completed baseline assessment and will allocate the participant IDs to either the usual care group or the intervention group based on the randomisation plan.

## Study Groups

Participants will be randomly allocated to one of two groups: weight loss support intervention group or usual care group.

### 5.3.1 Intervention group

The weight loss intervention will use a combined approach of increasing physical activity, reducing energy intake and behaviour change strategies. The intervention will be delivered entirely over the telephone by lifestyle coaches (who will be Accredited Practising Dietitians with additional study-specific training in exercise promotion). The intervention will be delivered over 12 months, with an initial intensive 6-month phase involving 16 calls (6 x weekly calls, 10 x fortnightly calls) followed by a 6-month maintenance-enhancement phase involving 6 monthly calls. Telephone calls will be scheduled based on participant preference (day vs. night). Participants will also receive a detailed workbook, set of digital scales, measuring tape, pedometer, kilojoule/calorie counter book and self-monitoring diary, which will be referred to over the 12-month intervention. Intervention participants will also be posted the same brochures and newsletter that the usual care participants receive (see below).

Participants will be encouraged to aim for weight loss of between 5-10% of their starting body weight. The physical activity component of the intervention includes both aerobic and resistance exercises, consistent with physical activity guidelines for cancer survivors. Women will be encouraged to slowly work towards a target of 30 minutes of moderate-level activity per day (210 minutes per week) and 2-3 sessions of resistance exercise per week. For diet, participants will be encouraged to reduce energy intake by 2000kJ. Participants will be prescribed a recommended kilojoule intake (between 5,000 – 7,500 kJ/day) based on age and baseline weight. Coaches will provide individualised advice including improving portion control, reducing energy density and eating regular meals along with kilojoule counting to achieve this energy reduction. In addition, participants will be encouraged to aim for total fat intake < 30% of energy, saturated fat intake < 7% of energy, 5 serves per day of vegetables and 2 serves per day of fruit. Both coach and participant will be provided with detailed feedback on the participant’s baseline and follow-up assessments (body composition, dietary intake, physical activity, blood test results) to monitor progress.

The behavioural component of the intervention will be guided by Social Cognitive Theory emphasising self-monitoring, goal setting, problem solving, social support, stimulus control, positive self-talk and self-reward. Coaches will use a motivational interviewing counselling style. The protocol for each call will include: assessment of progress; problem-solving; advice/education; collaborative goal-setting; and development of a behaviourally-specific action plan.

In addition, participants may choose to receive supplementary mobile telephone SMS (short-messaging service) from their Lifestyle Coach. As these SMS are optional, there is no set schedule of timing or content. These SMS are designed to provide additional support for achieving goals set during the telephone calls.

### 5.3.2 Usual Care group

Participants in the usual care group will continue to receive their standard medical care. In addition, these participants will be posted written materials after each of their study assessments (baseline, 6-months, 12-months, 18-months). These written materials will include brief feedback from their study assessment, off-the-shelf brochures and a study newsletter.

## Blinding

The group allocation sequence will be concealed from staff involved with participant recruitment (group allocation will be conducted by a staff member not involved with the study). Once allocated to the study group, the project manager and participants will not be blinded to the group allocation (as is the case with most lifestyle based interventions). Staff involved with data collection will remain blinded to the participants’ group allocation.

## Duration of treatment/ study

The Living Well after Breast Cancer study will continue recruiting patients into the study until a total of 160 participants have been randomised. After this recruitment target has been reached, no further enrolment will be possible and hospital sites will be informed to stop informing patients about the study. It is anticipated, that the accrual target will be reached by December 2014. The intervention and initial data collection is anticipated to be completed by December 2015. Furthermore, with a six-month follow-up, it is anticipated that final data collection will be completed by October 2016. See timeline below for an outline of anticipated milestones:

|  | **2012** | | | | **2013** | | | | **2014** | | | | **2015** | | | | **2016** | | | |
| --- | --- | --- | --- | --- | --- | --- | --- | --- | --- | --- | --- | --- | --- | --- | --- | --- | --- | --- | --- | --- |
| Develop study protocols, materials & database |  |  |  |  |  |  |  |  |  |  |  |  |  |  |  |  |  |  |  |  |
| Ethics & site specific approval |  |  |  |  |  |  |  |  |  |  |  |  |  |  |  |  |  |  |  |  |
| Participant recruitment |  |  |  |  |  |  |  |  |  |  |  |  |  |  |  |  |  |  |  |  |
| Data collection & intervention delivery |  |  |  |  |  |  |  |  |  |  |  |  |  |  |  |  |  |  |  |  |
| 6-month follow-up data collection |  |  |  |  |  |  |  |  |  |  |  |  |  |  |  |  |  |  |  |  |
| Analysis and reporting |  |  |  |  |  |  |  |  |  |  |  |  |  |  |  |  |  |  |  |  |

